### 2.9 Safety control

Acupuncture-related adverse events such as fainting, pain, bleeding, and infections will be recorded in detail and addressed promptly. Serious adverse events will be recorded by the researcher and reported to the individual in charge of the study and the ethics committee within 24 h. The patients will receive treatment until full recovery.

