## 2 Methods and analysis

### 2.1 Study design

This is a prospective, multicenter, randomized, single-blind trial with two parallel groups involving patients with stable COPD. As shown in Figure 2, sociodemographic data will be collected, and participants will complete symptom questionnaires and undergo magnetic resonance imaging (MRI) before and after the 8-week intervention period. Patients will be followed up for 12 months via telephone interviews to perform COPD assessment test (CAT) and record COPD exacerbations. The exact timing of each outcome measurement is presented in Table 1.

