#### 2.2.4 Withdrawal criteria

During the intervention period, enrolled participants will be withdrawn from the study if they (1) experience serious adverse reactions or unexpected events that prevent continuing participation; (2) experience serious complications or a deterioration in their condition requiring urgent treatment; (3) express a request to withdraw from the clinical trial; or (4) express the intent that do not want to complete the planned treatment.

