### 2.3 Randomization and blinding

Participants will be assigned in a ratio of 1:1 to undergo acupuncture at acupoints on the disease-affected meridian (DAM) or at non-acupoints on the non-affected meridian (NAM). The randomization sequence will be strictly executed according to the random number table generated by a third party; the randomization list will be blinded to other researchers or patients. Acupuncturists will be informed of the grouping to allow correct needle placement.

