### 2.5 Intervention

Participants will be randomly categorized into two parallel groups to undergo acupuncture at acupoints on the DAM or non-acupoints on the NAM for 8 weeks (every 2^nd^ day, three times a week). The six standardized acupoints on the DAM are as follows: (1) EX-B1 (Dingchuan), (2) BL13 (Feishu), (3) BL20 (Pishu), (4) BL23 (Shenshu), (5) LU7 (Lieque), and (6) ST36 (Zusanli) (Table 2). The six non-acupoints on the NAM have been designed to be 2.0 cun away from the acupoints on the DAM listed above (Figure 3). Acupuncture will be performed on patients in the prone position, using disposable stainless-steel needles inserted into the disinfected skin. The locations, directions, and depths of needle insertion are presented in Table 2. Minor stimulation, achieved by lifting and thrusting the needles along with thrusting and rotating the needle sheath, will be applied to produce the sensation known as deqi (a feeling of soreness, numbness, distention, or radiation, which is considered effective). Acupuncture needles will be inserted at the intended acupoints for 30 min.

**Table 2 T2:** Location of acupoints on the disease-affected meridian.

**Acupoints**	**Location**	**Depth**	**Direction**
Dingchuan (EX-B1)	On the back of the neck, 0.5 cun apart from the midpoint of the lower edge of the spinous process of the seventh cervical vertebra	0.5–1.0 cun	Vertically puncture or the needle point toward the spine
Feishu (BL13)	On the back, 1.5 cun apart from the spinous process of the third thoracic vertebra	0.5–0.8 cun	Oblique puncture
Pishu (BL20)	On the back, 1.5 cun apart from the spinous process of the eleventh thoracic vertebra	0.5–0.8 cun	Oblique puncture
Shenshu (BL23)	1.5 cun apart from the spinous process of the second lumbar vertebra	0.5–1.0 cun	Vertically puncture
Lieque (LU7)	On the radial side of the forearm and above the radial styloid process, between the brachioradialis muscle and the abductor pollicis longus tendon, 1.5 cun above wrist crease	0.2–0.3 cun	Upward oblique puncture
Zusanli (ST36)	On the outside of the shank, 3 cun below Dubi^*^ and a thumb lateral to the anterior tibial ridge	1.0–2.0 cun	Vertically puncture

^*^Dubi (ST35): when the knee is bent at a right angle, the acupoint is located at the concave position on the outer side of the patellar ligament of the knee joint.

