### 2.8 Statistical analysis

Qualitative variables will be expressed as numbers (percentages), and quantitative variables will be expressed as mean (standard deviation) or median (interquartile range [25%−75%], q1–q3). All efficacy evaluation data will be summarized according to the full analysis set and the per-protocol set. For safety analysis, the safety set will include all randomized participants who received at least one interventional treatment. A paired *t*-test or Wilcoxon signed-rank test will be conducted to compare the outcomes at baseline with those after the 8-week intervention period and during follow-up within a group. Analysis of covariance will be performed to compare the results after acupuncture and during follow-up between the groups. Exercise intensity will be adjusted to assess post-exercise dyspnea. Data will be analyzed using SPSS software version 26.0 (IBM Corporation, Armonk, NY, USA), and statistical significance will be set as a *p*-value of < 0.05.

Metadata from DICOM files will be converted to BIDS using HeuDiConv. fMRIPrep software version 21.0.4, a combination of tools from common software packages including FSL, ANTs, FreeSurfer, and AFNI, was developed by the laboratory of Russ Poldrack and the Stanford Center for Reproducible Neuroscience and will be used to perform minimal data preprocessing, including skull stripping, motion correction, segmentation, co-registration, and normalization. Motion artifacts will be removed automatically using independent component analysis (40). Subsequently, graph theory-based or data-driven approaches will be used to compare the differences between the DAM and NAM groups.

PANDA, a MATLAB toolbox that can be downloaded from https://www.nitrc.org/projects/panda/ and is based on MATLAB R2016a in the Ubuntu 16.04 operating system, will be used to analyze brain diffusion images. The coupling value between the functional connection matrix and the structural joint matrix will be calculated and correlated with clinical symptoms.

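### Section 2.9 ties recording of non-serious adverse events to their being acupuncture-related, so the non-serious harm tally may be under-counted in both arms

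*Protocol article*

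**What the plan says.** Adverse-event recording is set out in section 2.9, in two streams.

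- Events limited by cause: "Acupuncture-related adverse events such as fainting, pain, bleeding, and infections will be recorded in detail and addressed promptly".
- Serious events, with no condition on cause: "Serious adverse events will be recorded by the researcher and reported to the individual in charge of the study and the ethics committee within 24" hours.

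Section 2.8 fixes the safety population: "the safety set will include all randomized participants who received at least one interventional treatment". It states no between-arm safety comparison or test.

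Worsening of the disease is picked up elsewhere under two other labels. One is an outcome, in section 2.1: "Patients will be followed up for 12 months via telephone interviews to perform COPD assessment test (CAT) and record COPD exacerbations". Table 1 places exacerbation at baseline, 8 weeks, and 6, 9 and 12 months. The other is a reason for withdrawal, in section 2.2.4, for patients who "experience serious complications or a deterioration in their condition requiring urgent treatment".

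On needling, Table 2 in section 2.5 includes points at thoracic level on the back, for example Feishu: "On the back, 1.5 cun apart from the spinous process of the third thoracic vertebra". The control arm is needled too: "The six non-acupoints on the NAM have been designed to be 2.0 cun away from the acupoints on the DAM listed above". On knowledge of the arm, section 2.3 says: "Acupuncturists will be informed of the grouping to allow correct needle placement". The same section withholds the randomization list from other researchers and from patients.

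**The concern.** The usual order is to record an event first and judge its cause second. The wording of section 2.9 reverses this for non-serious events, because relation to acupuncture is part of the definition of what is recorded. The article gives no criteria for that judgement and does not name who makes it.

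The order matters more here than in most trials. Breathlessness is the main symptom of the disease and also the primary outcome (section 2.6.1). When a patient is more breathless or has chest discomfort after a session, the disease is a ready explanation. The four examples in section 2.9 are faints, pain, bleeding and infection, and none of them prompts staff to consider a respiratory event. That needling at the thoracic back could cause respiratory symptoms is an anatomical inference and not a statement in the article. The recording gap exists without it.

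What is at stake is the completeness of the non-serious harm data. Section 2.8 sets the denominator for safety, while section 2.9 filters the numerator. Events not written down at the time cannot be reliably recovered later.

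**Working it through.** The point is textual, and the article has no safety figure to reproduce. The first step traces where a respiratory event after a session, during the 8 treatment weeks, would be recorded under the rules as written.

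| Event | Attributed to needling? | Where it is recorded |
|---|---|---|
| Serious | Yes or no | Serious adverse event, section 2.9 |
| Non-serious | Yes | Acupuncture-related event, section 2.9 |
| Non-serious | No, taken for an exacerbation | Exacerbation outcome, sections 2.1 and Table 1 |
| Non-serious | No, and not called an exacerbation | No provision in the article |
| Deterioration needing urgent treatment | No | Withdrawal under section 2.2.4; also a serious event if it meets that definition |

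The third row is misclassification: the event is kept, but outside the harm tally. The fourth row is loss. Nothing in the article links the exacerbation or withdrawal records back to the adverse-event record, or to the time since the last session.

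**Direction.** Let p be the true risk of a non-serious event and c the share that passes the relatedness judgement. The recorded risk is p × c.

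- If c is the same in both arms, both tallies fall by the same factor. The ratio between arms is unchanged and the absolute counts are too low.
- The contrast is distorted only if c differs by arm. The article neither states nor excludes that.

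**Scale, for illustration only.** N = 90 comes from section 2.4. The values of p and c are assumptions, because the article gives neither. Expected recorded patients = 90 × p × c. Chance of recording none = (1 − p × c)^90.

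| Assumed p | c = 100% | c = 50% | c = 25% |
|---|---|---|---|
| 2% | 1.8 expected; none 16.2% | 0.9; none 40.5% | 0.45; none 63.7% |
| 5% | 4.5 expected; none 1.0% | 2.25; none 10.2% | 1.1; none 32.2% |
| 10% | 9.0 expected; none under 0.1% | 4.5; none 1.0% | 2.25; none 10.2% |

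Worked cell: p = 5%, c = 50% gives p × c = 0.025, 90 × 0.025 = 2.25 expected, and 0.975^90 = 0.102.

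The table shows how quickly an empty tally becomes compatible with a real risk in a trial of this size. It does not estimate what will happen.

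**The case against.** The strongest reply is that section 2.9 says what will be recorded and does not say that nothing else will be. The examples are open-ended, and a journal article commonly leaves adverse-event definitions and form fields to the full protocol. This stands in part: exclusivity is inferred, and the full protocol may record more. But the section is not simply silent. It puts a condition on cause for one stream and drops it for the other in the next sentence, so a site following the text would apply the distinction.

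A reader might also infer more than the article supports.

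- *That serious needling injuries could be lost.* They are recorded whatever the cause. The withdrawal route in section 2.2.4 concerns urgent deterioration, which is visible and would often be serious as well.
- *That events taken for disease vanish.* Exacerbations are recorded in both arms without regard to cause.
- *That the between-arm safety comparison is biased.* No such comparison is stated, both arms are needled, and the article does not say that acupuncturists, who know the arm, judge relatedness. Differential judgement is possible but not shown.
- *That injury to the lung or pleura is the harm most likely to be filtered out.* The article says nothing about such injury and gives no basis for ranking harms. Table 2 specifies oblique insertion at both thoracic back points, Feishu and Pishu.
- *That the trial would report acupuncture as safe because of this rule.* That needs event rates and capture shares that the article does not give.

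**Conclusion.** The point holds for non-serious events. As written, section 2.9 makes attribution to needling a condition of recording, with no stated assessor or criteria. A non-serious respiratory event in this population could be filed as an exacerbation or not recorded at all. The likely effect is under-counting of non-serious harm in both arms. A difference between arms would require relatedness to be judged differently by arm, which the article does not establish. Serious events are not affected.

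The size cannot be derived from the article. The conclusion assumes that section 2.9 is followed as worded and that the full protocol does not widen it. It does not depend on any particular injury mechanism. The change is worth making before or during data collection, because it is cheap and the lost data cannot be reliably rebuilt.

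**What to change.** Reword section 2.9 and the case-report form as follows.

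1. Record all adverse events in both arms, from first needling to Visit 2, whatever the presumed cause, with the time since the last session.
2. Enter relation to needling afterwards, as a separate field, by researchers from whom the allocation is already withheld under section 2.3.
3. Cross-check every event filed as an exacerbation, or as deterioration under section 2.2.4, against the adverse-event record.
4. Report all events, and related events, by arm in the safety set.

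If the full protocol already does this, one corrected sentence in section 2.9 is enough. The cost is a form and wording change, with more entries for minor COPD events. No extra visit or procedure is needed. The change concerns recording only and does not touch clinical management.

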## 3 Discussion

The recognized treatment effects of acupuncture on dyspnea in COPD are acknowledged in the COPD guidelines; however, its clinical application has been hampered by the low quality of evidence supporting its use and the lack of mechanistic studies. This randomized controlled trial aims to (1) conduct a well-designed 8-week acupuncture treatment program to observe its clinical efficacy in patients with stable COPD and to identify the location and pattern of brain activities related to dyspnea before and after treatment via functional and structural neuroimaging; (2) to explore the neural mechanisms of exertional dyspnea in patients with COPD via brain MRI using several graph theory-based or data-driven methods; and (3) to explore the comprehensive impact of acupuncture on dyspnea in multiple dimensions, particularly the affective dimension.

In this study, the acupoints commonly used for the treatment of COPD include Zusanli, Dingchuan, Lieque, Feishu, Pishu, and Shenshu (41). Acupuncture on Dingchuan can reduce the heart rate and dyspneic sensation in acute exacerbations of COPD and improve lung function in terms of forced expiratory volume in 1 s in patients with asthma (42, 43). Acupuncture on Zusanli, Pishu, Feishu, and Shenshu has been shown to improve pulmonary function and CAT scores and suppress inflammation in COPD (29, 44, 45). Acupuncture on Lieque and Zusanli has been reported to reduce nicotine cravings, and activation of the ACC, insula, and prefrontal cortex was found to be related to acupuncture (46). Stimulation of Zusanli evokes long-lasting activation of the supplementary motor cortex and deactivation of limbic/paralimbic and subcortical regions; the effect on these regions was extensive, and they were identified as network hubs related to the regulation of the secondary somatosensory cortex, emotion, and pain (23, 26, 47–49). Acupuncture on Zusanli improved the symptoms of functional dyspepsia by modulating the functional connectivity of the DMN (50). However, the target brain regions regulated by acupoints and the cumulative effects of stimulation were not determined in this randomized controlled trial on dyspnea.

Acupuncture, an important facet of traditional Chinese medicine, has demonstrated clinical efficacy in many conditions, including pain, mood disorders, and stroke, by modulating neural responses in the brain (51–53). Brain activation leads to enhanced blood flow, blood volume, and oxygen saturation in the cerebrum, thereby increasing deoxyhemoglobin levels, which is proportional to the magnetic resonance signal on functional MRI. The involvement of the sensorimotor and corticolimbic structures, which contributes to motor cognitive and emotional processing, in dyspnea perception is widely recognized (4, 25, 54). Among the brain areas related to dyspnea in COPD, the insular cortex is the most consistently reported region of sensory perception, followed by the amygdala, ACC, supplementary motor area, prefrontal cortex, and thalamus, suggesting that different neuronal networks are involved in dyspnea perception (55). According to the Embodied Prediction Interoceptive Coding and Neurovisceral Integration models, limbic cortices can generate predictions by integrating past experiences and updating through comparison with incoming sensory inputs, with the perception of breathlessness derived from the processes of interaction and comparison (56). Objective measures of disease are based on the balance between sensory inputs and predictions; factors such as effects and expectations can disrupt this balance and increase the perception of breathlessness (56). For example, pulmonary rehabilitation reduces dyspnea in patients by modulating the activity of expectation-related brain regions, such as the AI, ACC, and prefrontal cortex. Therefore, we hypothesize that acupuncture may modulate the activity of corticolimbic brain regions, such as the AI, ACC, and prefrontal cortex, to maintain the balance of predictions, thereby directly reducing dyspnea.

Anxiety or depression is experienced by 30%−40% of patients with COPD (57, 58). A self-perpetuating cycle of breathlessness and anxiety occurs in which breathlessness triggers anxiety, which in turn aggravates dyspnea (59). Fatigue and depression influence the perception of dyspnea by acting on the lateral prefrontal cortex, whereas anxiety can impair the sensitivity of resistive respiratory sensation (22, 60). In COPD patients, increased dyspnea is associated with anticipatory neural activation of the hippocampus, insula, and amygdala, which play key roles in emotional enhancement processes and are related to increased levels of anxiety and depression (61, 62). Therefore, the management of dyspnea-related anxiety and depression in patients with COPD has been investigated for its ability to attenuate the perception of dyspnea. Pulmonary rehabilitation has been reported to be the most effective treatment for dyspnea in patients with stable COPD, with a significant reduction in symptoms of depression and anxiety (63, 64). Pulmonary rehabilitation targets the brain network, including the amygdala, hippocampus, ACC, AI, and superior frontal gyrus, modulating the functions of cognitive control, symptom perception, and sensory integration; this modulation may lead to improved cognitive behavioral therapy outcomes for anxiety (65, 66). Another study reported that pulmonary rehabilitation reduced breathlessness–anxiety, which was related to lower activation of attention regulation and motor network function (67). Owing to the substantial overlap of cerebral activation regions and neural functions between anxiety and acupuncture stimulation, we hypothesize that acupuncture may modulate the activity of the lateral prefrontal cortex, hippocampus, ACC, or other brain regions to alleviate dyspnea-specific anxiety and depression and indirectly reduce breathlessness in COPD patients.

Exertional dyspnea is a major symptom of COPD and may be caused by dynamic hyperinflation during exercise (68). The Borg Dyspnea Scale, a measuring tool used during the 6MWT, can identify dynamic hyperinflation in patients with moderate-to-severe COPD with high reliability (69, 70). Exertional dyspnea during the 6MWT may be caused by a mismatch between central drive and mechanical response (71), and it has also been shown to be associated with activation of the prefrontal cortex in COPD (72). A study on cortical hemodynamics in patients with COPD suggested a stronger correlation between the premotor cortex and exertional dyspnea (73). Similar results have been observed in studies on dyspnea in healthy individuals (74). Therefore, in this study, an MRI will be performed after the 6MWT to explore the mechanisms of exertional dyspnea in the brain.

Depression is considered to be associated with more severe breathlessness, and anxiety plays a crucial role in the interplay between dyspnea and depression (75, 76). The unique connection between dyspnea and acute anxiety is considered to depend largely on subjective feelings (77), which are influenced not only by exteroception but also by interception. Interceptive awareness is a set of reciprocal afferent/efferent circuits that can integrate incoming information and engage in body signal regulation, with perceptual accuracy as a component (78). Anxiety sensitivity may reduce the stability of the Bayesian sensory perception system and increase misunderstanding of symptoms and dyspnea variability (28). Different levels of anxiety indicate different AI activities (79). A recent study suggested that AI and the pre-supplementary motor area are potential candidate brain regions for performing self-corrective functions (80). Thus, we assume that AI is key to the impact of anxiety on dyspnea and will explore the functional connections between AI and other brain regions related to exertional dyspnea for explaining the potential mechanism underlying the effects of anxiety on exertional dyspnea in patients with stable COPD.

To the best of our knowledge, this study is the first to investigate the neurobiological mechanisms of acupuncture for the treatment of dyspnea in patients with COPD. Importantly, non-acupoints on the NAM have been included as a placebo control. In this study, various dyspnea assessment scales were used before and after exercise and acupuncture. Additionally, diffusion tensor imaging and functional MRI data were collected to investigate the mechanisms of exertional dyspnea and its emotional impact on patients with stable COPD. Since dyspnea is a complex experience that can be caused or influenced by many factors and dimensions, we evaluated the effects of acupuncture on dyspnea from multiple aspects, including emotions and quality of life.

### 3.1 Limitations

This study has some limitations. The use of the 6MWT for exercise may induce different levels of exercise intensity in different patients, potentially resulting in varied levels of dyspnea. We compared exercise intensity and adjusted for the outcome of dyspnea, if needed. Furthermore, dyspnea in the ventral, frontal, and medial temporal regions could induce susceptibility artifacts on MRI, which may affect the results (81, 82). Therefore, we performed independent component analysis to automatically remove motion-induced artifacts.

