### 2.7 MRI

Participants will undergo MRI four times, performed using a 3.0 T superconductor (Magnetom Skyra; Siemens Healthineers, Erlangen, Germany). At baseline, resting-state MRI will be performed after symptom assessment, and post-exercise MRI will be performed immediately after the 6MWT to capture images during dyspnea. After the intervention period, resting-state and post-exercise MRI will be repeated. While undergoing an MRI scan, the participants will be required to maintain head and neck stability and keep their eyes open. A whole-brain anatomical image consisting of 192 sagittal slices with a thickness of 1 mm will be collected using a T1-weighted 3D sequence with the following parameters: repetition time = 2,300 ms, echo time = 2.26 ms, flip angle = 8°, voxel size = 1 × 1 × 1 mm, and inversion time = 900 ms. Functional MRI will be performed using an echo-planar imaging sequence with the following parameters: repetition time = 2,000 ms, echo time = 30 ms, flip angle = 70°, voxel size = 2 × 2 × 2.5 mm, and number of slices = 54. In addition, diffusion tensor imaging will be performed using the following parameters: repetition time = 5,100 ms, echo time = 80 ms, and voxel size = 1.7 × 1.7 × 2 mm.

Two experienced radiologists will review all images to identify abnormalities including brain damage, structural brain lesions, and artifacts.

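### The remedy offered for susceptibility artifact is a motion step, and no described step corrects static signal loss or distortion in areas that overlap hypothesised brain regions

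*Protocol article*

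**What the plan says.** Section 3.1 (Limitations) of the protocol article names the threat: "dyspnea in the ventral, frontal, and medial temporal regions could induce susceptibility artifacts on MRI, which may affect the results". The next sentence gives the response as a consequence of it: "Therefore, we performed independent component analysis to automatically remove motion-induced artifacts".

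Section 2.8 (Statistical analysis) gives ICA the same purpose: "Motion artifacts will be removed automatically using independent component analysis". The rest of the fMRIPrep work is described as "minimal data preprocessing, including skull stripping, motion correction, segmentation, co-registration, and normalization".

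Section 2.7 (MRI) lists three acquisitions: a T1-weighted anatomical image, an echo-planar functional series and diffusion tensor imaging. Two radiologists review all images to "identify abnormalities including brain damage, structural brain lesions, and artifacts".

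Section 3 (Discussion) states where effects are expected. For the direct pathway, "acupuncture may modulate the activity of corticolimbic brain regions, such as the AI, ACC, and prefrontal cortex". For the affective pathway, "acupuncture may modulate the activity of the lateral prefrontal cortex, hippocampus, ACC, or other brain regions".

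**The concern.** The threat and the remedy are different problems. Susceptibility artifact in echo-planar imaging arises from magnetic field inhomogeneity. It shows as lost signal and as tissue displaced from its true position. ICA denoising separates a recorded time series into components and removes those that look like motion. It acts on fluctuation over time. It cannot recover signal that was never recorded, and it does not move displaced tissue back.

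This matters because the imaging carries the trial's mechanistic questions. Hypotheses 2 to 4 in section 1 concern structure and connectivity in specific brain regions. If signal is weak or misplaced in a node, a null result there may reflect the measurement and not the biology. A reader of section 3.1 could also take the threat to have been dealt with by a step that does not address its static part.

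**Working it through.** No arithmetic applies. The documents give no readout time, field inhomogeneity or extent of signal loss, so the check sets the sections side by side.

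1. **Threat against remedy.** Section 3.1 names susceptibility artifact and responds with removal of motion-induced artifacts. Section 2.8 gives ICA no purpose beyond motion. The two do not match.

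2. **Other preprocessing (2.8).** Five steps are listed. Skull stripping and segmentation label tissue. Motion correction realigns volumes to one another. Co-registration and normalization align images to the anatomy and to a template. None is described as susceptibility distortion correction, and none restores lost signal.

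3. **Acquisition (2.7).** "Functional MRI will be performed using an echo-planar imaging sequence", with a 2 × 2 × 2.5 mm voxel and an echo time of 30 ms. No field map or reversed phase-encoding image is mentioned.

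4. **Image review (2.7).** The radiologists identify artifacts. No correction or exclusion rule is attached to what they find.

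5. **Overlap with the hypotheses.**

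| Region hypothesised (section 3) | Within the areas named in 3.1? |
|---|---|
| Hippocampus | Yes, medial temporal |
| Prefrontal cortex, including lateral | Broadly, frontal |
| Anterior cingulate cortex | Not named |
| Anterior insula | Not named |

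The amygdala is medial temporal too, but it appears in the supporting literature and not in the two hypothesis sentences quoted above.

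6. **Which comparisons are exposed.** As a simplification, let the recorded signal in a node be *a* × *m*, where *m* is the true quantity and *a* (between 0 and 1) is the fraction that survives the artifact.
   - *Between randomized groups.* Static artifact is expected to be alike in both arms, so *a* is common. The observed difference is *a*(*m*₁ − *m*₂). A true difference is shrunk, and a true zero stays zero. The cost is sensitivity, and localisation where tissue is displaced.
   - *Rest versus post-exercise (hypothesis 4).* The post-exercise scan follows the walking test immediately, so breathing differs between the two states, and section 3.1 itself ties the artifact to dyspnea. If *a* differs by state, then with equal true values *m* the observed difference is (*a*_rest − *a*_exercise)*m*, which need not be zero. Bias is possible.
   - *Function-structure coupling (2.8).* The coupling value requires functional and diffusion nodes to cover the same tissue. Uncorrected displacement would weaken that match.
   - *Primary outcome (2.6.1).* This is a clinical dyspnea score and does not depend on the images.

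**The case against.** The best defence is that this is a condensed article. The preprocessing list is introduced as examples, the acquisition section gives headline parameters, and the full protocol may contain a field map or a distortion correction. The named pipeline can perform one, and nothing says it is switched off. This stands against a stronger reading, that the data remain distorted. A reader might infer that, but the documents show only that no described step corrects the artifact. It does not rescue the sentence in section 3.1, which would still offer the wrong remedy for the problem it names.

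Second, section 3.1 attributes the artifact to dyspnea. If a breathing-linked, time-varying component is meant, ICA could remove part of it. That is fair, and it limits the criticism to static signal loss and geometric distortion.

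Third, section 3.1 sits under Limitations, says the results may be affected and never says the problem is solved; the radiologist review is also a real quality check. Both are true. Yet the response is worded as following from the threat, and the review identifies artifacts without correcting them.

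Fourth, a reader might infer that the artifact will produce a false difference between the groups, or that the trial's imaging biomarker is compromised. Neither is supported. Static artifact should affect both randomized arms alike, and the article defines no single imaging biomarker. The regions it stresses most, the anterior cingulate cortex and anterior insula, are not named in section 3.1.

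**Conclusion.** The point holds in a limited form. The stated remedy addresses motion. The stated threat is susceptibility artifact. No step described in sections 2.7 and 2.8 covers its static part, in areas that overlap the hippocampus and, broadly, the prefrontal cortex. This is an error in what the article states as well as an absence of detail.

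The size cannot be given in millimetres or percent signal loss. Any such figure would rest on assumed scanner settings, since the voxel size alone does not determine displacement. In kind, the expected harm is lost sensitivity and localisation in the comparison between groups, with possible bias in the rest versus post-exercise contrast and in the coupling measure. The clinical efficacy conclusion is untouched.

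The verdict assumes that static artifact is unrelated to group, which randomization makes reasonable, and that the article's description of processing is what a reader has to go on. Confidence is high for the mismatch and lower for its practical effect. It should be corrected, but it does not undermine the trial's primary question.

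**What to change.** In sections 2.8 and 3.1:

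- Present ICA as a motion step only, and remove the wording that makes it the answer to susceptibility artifact.
- Apply one susceptibility distortion correction within fMRIPrep, by the same method, to every scan of every participant. If field maps were not acquired at all sessions, use the fieldmap-less option throughout. Mixing methods between baseline and week 8 could build a processing difference into the before-after contrast.
- Add a temporal signal-to-noise or signal-loss mask, defined blind to group, because distortion correction does not recover lost signal. Make no claim of presence or absence of effect in nodes that fail it.
- If no correction is possible, state the artifact as an unmitigated limitation.

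If the full protocol already specifies a correction, stating it in 2.8 and rewording 3.1 settles that part.

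The cost is a setting in the pipeline already named, a mask step and some rewording, with no extra patients or visits. The downsides are small: some nodes will be declared not assessable, and fieldmap-less correction is approximate.
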